### Statistical methods

Data is anonymized and blinded before the analyses. Analyses are performed by a researcher not otherwise involved in the inclusion or randomization, data collection or handling. All statistical tests will be testing the null hypotheses assuming the two arms of the trial being equal based on corresponding estimates. Analysis of primary outcome on short-term learning will be started once all data has been collected for all individuals in the last included course. Analyses of long-term academic achievement will be started at end of follow-up.

Baseline characteristics including both course- and individual level information will be presented. Table 2 presents the available data on baseline.

**Table 2 Tab2:** Baseline patient characteristics of participants

VARIABLES AT COURSE LEVEL		
	Name	Practical Course in Systematic Review Technique in Clinical Research; Getting started: Writing your first manuscript for publication
	Setting	Online; Onsite
	Language	Danish; English
VARIABLES AT INDIVIDUAL LEVEL		
	Sex	Male; Female
	Education prior to PhD study	MD; MSc Public Health; University College + MSc; MSc Other
	Pre-test knowledge scores	0-25

We will use multivariate analysis for identification of the most important predictors (motivation, self-efficacy, sex, educational background, and knowledge) for best effect on short and long term. The results will be presented as risk ratio (RR) with 95% confidence interval (CI). The results will be considered significant if CI does not include the value one.

All data processing and analyses were conducted using R statistical software version 4.1.0, 2021–05-18 (R Foundation for Statistical Computing, Vienna, Austria).

If possible, all analysis will be performed for “Practical Course in Systematic Review Technique in Clinical Research” and for “Getting started: Writing your first manuscript for publication” separately.

Primary analyses will be handled with the intention-to-treat approach. The analyses will include all individuals with valid data regardless of they did attend the complete course. Missing data will be handled with multiple imputation [28]*.*

Upon reasonable request, public assess will be granted to protocol, datasets analysed during the current study, and statistical code Table 3.

**Table 3 Tab3:** Outcome framework, measurements and analyses

**Kirkpatrick**	**Term**	**Outcome**	**Tool**	**Measurement**	**Analysis**
Primary outcome					
Level 2 (Learning)	Short	Knowledge	Tested MCQ	25 questions with 3 integers	Mann–Whitney
Level 2 (Learning)	Short	Knowledge Passed	Tested MCQ	Binary	Fisher’s exact
Secondary outcomes					
Level 1 (Reaction)	Short	Motivation	Intrinsic Motivation Inventory	12 questions on 7-point Likert scale	Mann–Whitney
Level 1 (Reaction)	Short	Self-efficacy	Williams and Smith	1 question on 10 point Likert scale	Mann–Whitney
Level 1 (Reaction)	Short	Preference	Survey	Binary	Fisher’s exact
Level 4 (Results)	Long	Academic achievements	Google Scholar	Publications, citations, h-index, and i10-index	Kaplan Meyer and log rank test

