### Primary outcome

The primary outcome is short term learning (Kirkpatrick level 2).

Learning is assessed by a Multiple-Choice Questionnaire (MCQ) developed prior to the RCT specifically for this setting (Appendix 4). First the lecturers of the two courses were contacted and asked to provide five multiple choice questions presented as a stem with three answer options; one correct answer and two distractors. The questions should be related to core elements of their teaching under the heading of research training. The questions were set up to test the cognition of the students at the levels of "Knows" or "Knows how" according to Miller's Pyramid of Competence and not their behaviour [21]. Six of the course lecturers responded and out of this material all the questions which covered curriculum of both courses were selected. It was tested on 10 PhD students and within the lecturer group, revised after an item analysis and English language revised. The MCQ ended up containing 25 questions. The MCQ is filled in at baseline and repeated at the end of the course. The primary outcomes based on the MCQ is estimated as the score of learning calculated as number of correct answers out of 25 after the course. A decrease of points of the MCQ in the intervention groups denotes a deterioration of learning. In the MCQ the minimum score is 0 and 25 is maximum, where 19 indicates passing the course.

Furthermore, as secondary outcome, this outcome measurement will be categorized as binary outcome to determine passed/failed of the course defined by 75% (19/25) correct answers.

The learning score will be computed on group and individual level and compared regarding continued outcomes by the Mann–Whitney test comparing the learning score of the online and onsite groups. Regarding the binomial outcome of learning (passed/failed) data will be analysed by the Fisher’s exact test on an intention-to-treat basis between the online and onsite. The results will be presented as median and range and as mean and standard deviations, for possible future use in meta-analyses.

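### The plan gives two conflicting rules for students without a post-course score, and names no estimate to pool if scores are imputed

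*Protocol article*

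**What the plan says.** All the statements are in the protocol article.

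- Statistical methods gives three consecutive sentences. The first sets the principle: "Primary analyses will be handled with the intention-to-treat approach". The second says who is analysed: "The analyses will include all individuals with valid data regardless of they did attend the complete course". The third turns to gaps in the data: "Missing data will be handled with multiple imputation".
- The Primary outcome section defines the outcome as the number of correct answers out of 25 after the course, compared "by the Mann–Whitney test comparing the learning score of the online and onsite groups". For pass/fail (19 or more correct), "data will be analysed by the Fisher’s exact test on an intention-to-treat basis between the online and onsite".
- The results are to be shown as median with range and mean with standard deviation. No between-arm effect estimate is named for the learning score.
- The Primary outcome section calls pass/fail secondary, while Table 3 lists it under the primary outcome.
- The Sample size section allows for the loss of up to 2 of 12 students per course.

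**The concern.** The second and third sentences point to different sets of students for the primary analysis. One analyses the scores that exist; the other fills in those that do not. The named tests do not settle which is meant. They suit an available-case analysis as they stand, but after imputation they need a further choice that the plan does not make: which estimate is pooled, or how the P values are combined.

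At stake is whether the primary analysis is fixed in advance. Two analysts following the same text could analyse different students and report different P values. One analyst could also run both and choose. The analyst is external and blinded to arm, which limits this freedom but does not remove it, because both P values can be seen under masked labels.

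**Working it through.** **1. The two sentences applied to one student.** Take a consenting student with a baseline score and no post-course questionnaire.

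| Sentence applied | Is the student in the primary test? |
|---|---|
| Analyses include those with valid data | No |
| Missing data are multiply imputed | Yes, with an imputed score |

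The primary test has two inputs: setting, which is always known, and post-course score. Baseline score, sex and education do not enter it. If only students with a valid post-course score are analysed, imputation has nothing to do in this test, except perhaps to fill blank single items. The sentences can be reconciled for other variables, but not for a wholly missing primary outcome.

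**2. How many students this could concern.** The plan's 17% reproduces: 2/12 = 16.7%. Over the planned 20 courses of 12 that is 2 × 20 = 40 of 240 seats. This is a ceiling. It is a sample-size allowance, students who withdraw consent or ask to change setting leave the study, and class time is set aside for the tests.

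**3. What can be pooled.** Rubin's rules need an estimate Q and a variance U from each of M completed data sets. The total variance is T = mean(U) + (1 + 1/M)B, where B is the variance of Q between data sets. A bare P value supplies neither Q nor U. The Mann–Whitney test does correspond to an estimate, P(X>Y) + 0.5·P(X=Y), which has a variance.

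A simulation checked whether imputed data can be analysed this way. It had no true effect, 100 per arm, 17% missing, 20 imputations with baseline score in the imputation model, assumed score distributions, no clustering and 1,000 replicates.

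- Pooled Mann–Whitney estimate: 4.8% rejections at a nominal 5%.
- Median of the Fisher P values: 2.9%, which is conservative.

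Simulation error is √(0.05 × 0.95/1000) = 0.7 points. A workable analysis therefore exists, but both combining rules had to be supplied from outside the plan.

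**4. How much the choice of rule matters.** A second simulation had no true effect, 20 courses of 12, 2 missing per course, 10 imputations that ignored course, an assumed baseline correlation of 0.5 and 1,500 replicates (error √(0.05 × 0.95/1500) = 0.6 points).

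- The available-case and pooled-imputation Mann–Whitney tests disagreed on significance in 2.4% of data sets at intraclass correlation 0.02, and in 4.4% at 0.20.
- At 0.02, false positives were 7.1% and 7.0% under the two fixed rules, and 8.3% if the more favourable result was taken.

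The level near 7% comes from ignoring clustering. With 10 analysed per course the design effect is 1 + 9 × 0.02 = 1.18. The effective critical value is 1.96/√1.18 = 1.80, and the two-sided tail area beyond it is about 7.1%.

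**5. Imputing without course.** Two simulations imputed without course, analysed at course level and pooled. Type I error is compared with the same analysis of observed scores.

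| Intraclass correlation | First run: imputed (observed 5.1–5.3%) | Second run: imputed v observed |
|---|---|---|
| 0.02 (the plan's value) | 5.3% | 4.1% v 4.5% |
| 0.10 (assumed) | 5.9% | 6.9% v 5.5% |
| 0.20 (assumed) | 7.5% | 7.1% v 5.8% |

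No effect is detectable at 0.02. At the higher assumed values it is about 1 to 2 points.

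**The case against.** The strongest reply is that the valid-data sentence is about attendance. It follows the intention-to-treat sentence, and its main purpose is to keep students who missed part of the course. Imputation could then fill gaps such as a missing baseline score, and the imputation model and pooling rule may be in an analysis plan that is not shown.

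Much of this stands. The attendance statement is useful and should stay, and the lack of an imputation model in a condensed article is no fault. The reply does not help the primary test, though, which uses none of the variables that imputation would then fill. A further document could say which sentence governs, but it could not make both true for a missing post-course score.

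A reader might infer more than the document supports:

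- That nothing can be pooled, so the analysis cannot be carried out. Working step 3 shows otherwise, and a pass/fail risk ratio and the arm means can also be pooled.
- That the plan imputes without regard to course. It names no imputation model; that was an assumption of the simulations.
- That Fisher's exact test is part of the primary analysis. Only the layout of Table 3 suggests this.

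**Conclusion.** For the primary outcome the plan states two missing-data rules that conflict, and it names tests that do not say what is pooled. This is an ambiguity of moderate weight, not an unworkable analysis. Under the assumptions shown, the two readings disagree on significance in about 2% of null trials at the plan's intraclass correlation, and free choice between them adds about one point of false positives (8.3% against 7.0–7.1%). These figures use the full dropout allowance and would be smaller with the high retention that the protocol expects. The effect of imputing without course is not detectable at 0.02 and is no ground for the point. The change is still worth making, because one estimate can settle the missing-data rule, use the baseline score already collected and respect the cluster design.

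**What to change.** - State one rule for consenting students without a post-course score: imputed or not. Keep the statement that incomplete attendance does not exclude anyone, and reword only the phrase about valid data.
- Make the primary estimate the difference in mean post-course score from a linear mixed model with a random intercept for course, adjusted for baseline score and course title.
- If imputation is used, include setting and course in the imputation model and pool this estimate by Rubin's rules. Derive pass/fail (19 or more) from the imputed score and pool a risk ratio or risk difference.
- Report the available-case analysis as a sensitivity analysis.
- Bring the Primary outcome section and Table 3 into line with this, including the status of pass/fail.

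The mixed model is one coherent solution, not the only one; a pooled Mann–Whitney probability would also remove the ambiguity, but would leave clustering ignored. The cost is a change of analysis wording and a little more programming. No additional data are needed.

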### Oversight, monitoring, and adverse events

This project is coordinated in collaboration between the WHO CC (DEN-62) at the Parker Institute, CAMES, and the PhD School at the Faculty of Health and Medical Sciences, University of Copenhagen. The project leader runs the day-to-day support of the trial. The steering committee of the trial includes principal investigators from WHO CC (DEN-62) and CAMES and the project leader and meets approximately three times a year.

Data monitoring is done on a daily basis by the project leader and controlled by an external independent researcher.

An adverse event is “a harmful and negative outcome that happens when a patient has been provided with medical care” [29]. Since this trial does not involve patients in medical care, we do not expect adverse events. If participants decline taking part in the course after receiving the information of the course setting, information on reason for declining is sought obtained. If the reason is the setting this can be considered an unintended effect. Information of unintended effects of the online setting (the intervention) will be recorded. Participants are encouraged to contact the project leader with any response to the course in general both during and after the course.

The trial description has been sent to the Scientific Ethical Committee of the Capital Region of Denmark (VEK) (21041907), which assessed it as not necessary to notify and that it could proceed without permission from VEK according to the Danish law and regulation of scientific research. The trial is registered with the Danish Data Protection Agency (Privacy) (P-2022–158). Important protocol modification will be communicated to relevant parties as well as VEK, the Joint Regional Information Security and Clinicaltrials.gov within an as short timeframe as possible.

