### Interventions

Online course settings will be compared to onsite course settings. We test if the onsite setting is different to online. Online learning is increasing but onsite learning is still the preferred educational setting in a medical context. In this case onsite learning represents “usual care”. The online course setting is meetings in Zoom using the technicalities available such as chat and breakout rooms. The onsite setting is the learning facilities, at the Parker Institute, Bispebjerg and Frederiksberg Hospital, The Capital Region, University of Copenhagen, Denmark.

The course settings are not expected to harm the participants, but should a request be made to discontinue the course or change setting this will be met, and the participant taken out of the study. Course participants are allowed to take part in relevant concomitant courses or other interventions during the trial.

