### Assignment of interventions: allocation

Randomization will be performed on course-level. The courses are randomized by a computer random number generator [26]. To get a balanced randomization per year, 2 sets with 2 unique random integers in each, taken from the 1–4 range is requested.

The setting is not included in the course catalogue of the PhD School and thus allocation to online or onsite is concealed until 3–4 weeks before course commencement when a welcome letter with course information including allocation to online or onsite setting is distributed to the students. The lecturers are also informed of the course setting at this time point. If students withdraw from the course after being informed of the setting, a letter is sent to them enquiring of the reason for withdrawal and reason is recorded (Appendix 7).

The allocation sequence is generated by a computer random number generator (random.org). The participants and the lecturers sign up for the course without knowing the course setting (online or onsite) until 3–4 weeks before the course.

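### Apart from reasons for declining or withdrawing, the plan commits to recording unintended effects of the online setting but not of the onsite setting

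*Protocol article*

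**What the plan says.** Four statements in the protocol article bear on unintended effects.

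- **Recording rule** (Oversight, monitoring, and adverse events): "Information of unintended effects of the online setting (the intervention) will be recorded". The online setting is named; the onsite setting is not.
- **Declining the course** (same section): "If participants decline taking part in the course after receiving the information of the course setting, information on reason for declining is sought obtained". The next sentence adds: "If the reason is the setting this can be considered an unintended effect". Neither is limited to one arm.
- **Withdrawal after the setting is known** (Assignment of interventions: allocation): "a letter is sent to them enquiring of the reason for withdrawal and reason is recorded". This too applies whichever setting was allocated.
- **Spontaneous feedback** (Oversight, monitoring, and adverse events): "Participants are encouraged to contact the project leader with any response to the course in general both during and after the course". It is open to everyone, but the text does not say that such contacts are logged as unintended effects.

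The same section gives the general expectation: "Since this trial does not involve patients in medical care, we do not expect adverse events". The Interventions section treats onsite teaching as the usual-care comparator. It also says that a request to leave the course or to switch setting will be granted and the student removed from the trial, without mentioning a record of the reason.

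**The concern.** The trial asks whether the two settings differ, and Statistical methods sets a null hypothesis of equal arms. A record of unintended effects serves that question only if it is made in the same way in both arms. An unintended effect seen online cannot be attributed to the online setting unless one knows how often comparable problems arise onsite. Calling onsite the usual-care arm does not remove that need, because the comparator supplies the reference rate.

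The wording is also uneven within a single paragraph. The sentence defining a setting-related decline as an unintended effect is neutral between arms, and the recording sentence that follows it is not.

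The setting is known to students and lecturers, the project leader both collects the data and receives spontaneous reports, and the Background reports an impression that students saw online courses as second best. In an open trial an identical rule for both arms is the simplest protection against uneven ascertainment. At stake is a secondary, descriptive part of the eventual report.

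**Working it through.** The plan gives no figure for unintended effects, so there is nothing to reproduce. The check is a reading of the text by stage, followed by an illustration of which way uneven recording would push the result.

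**Step 1. What is promised for each arm at each stage**

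| Stage | Online | Onsite | Source |
|---|---|---|---|
| Declines or withdraws after learning the setting | Reason sought | Reason sought | Oversight; Allocation |
| Asks to leave the course or switch setting | Removed from the trial; recording rule names this arm | Removed from the trial; no recording rule | Interventions; Oversight |
| Takes the course and has a setting-related problem | Recorded | No commitment | Oversight |
| Contacts the project leader spontaneously | Invited | Invited | Oversight |

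The first and last rows are symmetric. The third is not, and the second is only partly so. Since the letter and the enquiry reach only students who decline or withdraw, they do not fill the third row. The open invitation might, but it depends on the student's initiative and is not described as a source of recorded data.

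**Step 2. Direction of any distortion (illustration only)**

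Inputs: 10 clusters × 12 participants = 120 seats per arm (Sample size). Event rates are assumptions, because the documents give none. Online capture is assumed complete. Let c be the share of onsite effects that is captured.

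Recorded difference = p_online − c × p_onsite

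Recorded counts = 120 × p_online and 120 × c × p_onsite

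| True rates (online, onsite) | c = 0 | c = 0.5 | c = 1 |
|---|---|---|---|
| 5%, 5% | 6 v 0, +5 points | 6 v 3, +2.5 points | 6 v 6, 0 |
| 5%, 10% | 6 v 0, +5 points | 6 v 6, 0 | 6 v 12, −5 points |
| 0%, 5% | 0 v 0, 0 | 0 v 3, −2.5 points | 0 v 6, −5 points |

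A positive value counts against online. Two things follow. First, the recorded difference equals the true difference in every row only when c = 1. For c below 1 it is shifted against online by (1 − c) × p_onsite. Second, its sign is not fixed: with partial capture onsite it can be positive, zero or negative. For setting-related withdrawals the text implies c near 1, subject to replies to the letter. For effects among students who take the course, c is unknown and nothing in the text secures it.

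**The case against.** A reader might infer something stronger: that the harms record exists for the online arm alone and must make online look worse whatever happens onsite. The documents do not support this.

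- The one unintended effect that the article defines is declining because of the setting, and the reason is sought in both arms. Withdrawal reasons are likewise recorded without limit by arm.
- Online would look worse than it truly does only where onsite effects occur and are incompletely captured. It would look worse than onsite in the record only if, in addition, at least one online effect is recorded.
- Table 3 lists no comparison of unintended effects. The implications for course planners in the Perspectives section rest on the learning and preference results.
- The hypothesis is two-sided, and the Background also gives a reason why current technology might favour online.

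All of this stands, and it limits the point.

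It can also be argued that other arm-neutral information exists. Presence is monitored in both groups (Strategies to improve adherence), and the general satisfaction evaluation, whose full content is not in the article text, may already ask about problems with the setting. That is fair, and the fix allows for it. It can be added that a journal article condenses the full protocol. This carries less weight here, because the restriction to online is written into the sentence and is not a detail left out.

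**Conclusion.** The point holds in a limited form. Reasons for declining or withdrawing are sought in both arms. Beyond those, the article commits to recording unintended effects for the online setting and makes no matching commitment for onsite. Effects arising among students who take the course could therefore not be compared fairly between settings.

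No size can be put on this from the documents. Under the assumed rates above, the recorded difference is shifted against online by between 0 and 10 percentage points, depending on the onsite rate (5% or 10%) and on how much is captured onsite; the upper end is 10% × (1 − 0). These figures illustrate the mechanism and are not estimates.

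Severity is low. The primary outcome, its analysis and the sample size are untouched, and no formal comparison of unintended effects is planned. The conclusion assumes that the recording sentence means what it says and that the end-of-course evaluation does not already collect setting-related problems in both arms. If it does, a correction of wording is enough.

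**What to change.** 1. Replace the recording sentence with: *Unintended effects of the allocated setting will be recorded in the same way in both arms.* This brings it into line with the arm-neutral handling of declines and withdrawals.
2. For any courses still to run, add one identical item to the end-of-course evaluation in both arms, asking whether the setting caused any problem and, if so, which. Omit this if the evaluation already has such an item.
3. Report the counts descriptively by arm, together with setting-related withdrawals.
4. For completed courses, report by arm what was actually collected and state that the recording rule named the online setting only. Keep these courses separate from any that used the common item.

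The cost is one sentence and at most one item in a survey that students are already asked to complete. Its reach may be small: inclusion opened in January 2022 and recruitment was expected to finish in April 2024, so a late item would cover few courses. For the rest, disclosure is the remedy available.
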